## **Group 3: children 12-47 months without allergy**

### **Visit 1, week 0, duration 30 min**

Families with children, 1-4 years without allergic disease and who are to undergo blood sampling for another reasons, e.g. prior to surgery at Astrid Lindgren Children's Hospital, Karolinska Hospital, are asked orally and via written information for participation in the control group. Signed consent is mandatory for participation in the study.

A questionnaire is filled in by the parent to ensure that the child does not have allergic problems. Blood sampling (20 ml) is taken for analysis of immunoglobulins and immunological markers (Table 1). Materials for submission of feces sampling are provided. Questions about quality of life will be answered by the parents.

### **Visit 2, 3 years after inclusion; duration 30 min/visit: sampling and history of allergies**

3 years after inclusion, a questionnaire is filled in by the parent to investigate if the child have developed allergic problems. Blood sampling (20 ml) is taken (Table 1). Materials for feces

sampling are provided before the visit in the invitation letter for the visit. Questions about quality of life will be answered by the parents.

### Data Collection

Each individual receives a unique code for identification. The results of the challenges and completed diaries signed consent forms, that are available in paper form are saved in binders stored at the Children's Research Center, Södersjukhuset in locked space until they are entered into the database. All data will be entered into a secure database (RedCap) with only code numbers as identification. In addition, web-based questionnaires and diaries are filled by the guardians directly into the database under code numbers. Analyzed data on blood and feces samples are entered into the database. A code key connecting the individual information and code numbers will be stored, locked in at the Research Center, Södersjukhuset's server, accessible only to the principal investigator, research physician and research nurse. The material will be saved for about 10 years.

**Table 1. Time points for blood samples, faecal samples and QoL questionnaires**

| Samples            | 1.
Baseline
visit | 2.
One year after
OIT start | 3.
Three years after
OIT start | 4.
At OFC after 4 weeks
without peanuts |
|---------------------------|----------------------------------|--------------------------------------------|-----------------------------------------------|--------------------------------------------------------|
| Blood, 20 ml per occasion | Group 1+2+3                      | Group 1+2                                  | Group 1+2+3                                   | Group 1                                                |
| Feces*                    | Group 1+2+3                      | Group 1+2                                  | Group 1+2+3                                   | Group 1                                                |
| QoL questionnaire         | Group 1+2+3                      | Group 1+2                                  | Group 1+2+3                                   |                                                        |

\* Fecal samples are submitted by the parents; sampling is done in the home by the parents saving a small amount of stool (5 ml) using a sampling kit. Information on the sample's preservation, freezing and stored cold during transport to the study center, will be received from the study center.

**Table 2a. Protocol for baseline peanut challenge (and for Group 2 also after 1 and 3 years)**

| Dose | Amount of peanut mixture*       | Amount of peanut protein, mg |
|-------------|----------------------------------------|-------------------------------------|
| 1           | 0,1 g mixture                          | 0,3                                 |
| 2           | 1 g mixture                            | 2,5                                 |
| 3           | 10 g mixture                           | 25                                  |
| 4           | 100 g mixture
(or 1g peanut butter) | 250                                 |

\*Mixture: 0.2g peanut butter mixed with 19.8g of something the child can eat

**Table 3a. Start of immunotherapy, mini up-dosing (for low doses)**

| Dose nr | Amount peanut protein, mg | Amount peanuts, mg | Amount peanut flour 10%* in mg (4,6% peanut protein) | Interval (min) |
|---------|---------------------------|--------------------|------------------------------------------------------|----------------|
| 1       | 0.8                       | 3.2                | 17                                                   | 30             |
| 2       | 1.5                       | 5.6                | 33                                                   | 30             |
| 3       | 3                         | 11                 | 65                                                   | 30             |
| 4       | 6                         | 22                 | 130                                                  | 30             |

\*Mix 1g Peanut powder with 9g oat flour

**Table 3b. Schedule for slow up-dosing: Starting dose is calculated from reaction dose at the baseline challenge**

| Dos nr | Amount of peanut protein, mg | Amount of peanut flour 10%* in mg (4,6% peanut protein) | Amount of peanuts, mg (one peanut approx. 800 mg) | Pieces of Bamba (700mg/piece, protein content 17,5%) | Interval, weeks | % increase |
|--------|------------------------------|---------------------------------------------------------|---------------------------------------------------|------------------------------------------------------|-----------------|------------|
| 4      | 3                            | 67                                                      | 11                                                |                                                      | 4               | 100        |
| 5      | 6                            | 133                                                     | 22                                                |                                                      | 4               | 100        |
| 6      | 12                           | 267                                                     | 44                                                |                                                      | 4               | 100        |
| 7      | 24                           | 533                                                     | 88                                                |                                                      | 4               | 100        |
| 8      | 32                           | 1067                                                    | 176                                               | 1/3                                                  | 4               | 100        |
| 9      | 48                           | 1578                                                    | 264                                               | 1/2                                                  | 4               | 50         |
| 10     | 95                           | 2111                                                    | 352                                               | 1                                                    | 4               | 33         |
| 11     | 144                          | 3200                                                    | 528                                               | 1,5                                                  | 4               | 50         |
| 12     | 190                          | 4222                                                    | 704                                               | 2                                                    | 4               | 33         |
| 13     | 238                          | 5289                                                    | 880                                               | 2,5                                                  | 4               | 25         |
| 14     | 285                          | 6333                                                    | 1056                                              | 3                                                    | 4               | 20         |

\*Mix 1g Peanut powder with 9g oat flour

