## Intervention substance

For the lower peanut OIT doses we will for practical reasons use peanut flour (peanøttmel, 50% protein content, Sukrin, Oslo, Norway) mixed with oat flour (Havremjöl glutenfritt, Urtekram, Midsona AB, Jylland, Denmark). For higher OIT doses (from 32 mg peanut protein) and the maintenance dose we will use “BAMBA” - a peanut-coated corn puff that dissolves in the mouth and contains 50% peanut and used in the LEAP study (Osem Food Industries, Shohan, Israel).

## Visits - groups 1 and 2

**Visit 1, screening visit, duration 1 hour:** the child and parents come to the Research Center at Sachs' Children and Youth Hospital for an information and screening visit. Written consent from both parents / legal guardians is mandatory to participate in the study. At the visit the families will be informed about the study design, follow-up schedule and adverse events that

may arise. A medical history on previous allergic reactions to peanuts and other background factors is collected. If necessary, the study physician will also review the medical records. Materials for fecal samples are provided.

**Visit 2, baseline challenge, duration 6 hours:** all children with a suspected peanut allergy, groups 1 and 2, undergo an open peanut challenge with peanut flour using (Table 2a). Before the start of the challenge, the child is examined by the physician according to a pre-set form. Only children free of infections and ongoing allergic symptoms may undergo challenge. For safety reasons, all children will receive a peripheral venous catheter after local anesthesia (EMLA). From the peripheral venous catheters, blood samples for immunoglobulins, blood status and immunological markers (20 ml) will be drawn (Table 1). Questions about quality of life will be answered by the parents. Observation time will be 2 hours after the last dose. If the child has undergone an equivalent challenge in the clinic within 1 year, no new challenge needs to be done.

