### **Group 1, Peanut Allergic Children Undergoing OIT Peanut, Slow Up-dosing**

#### **Visit 3, week 0, duration 6 hours: start immunotherapy:**

Clinical examination of the child is performed and noted in a standardized form. The peanut OIT starts with 1/4 of the dose (at least 3 mg of peanut protein) that gave the first reaction at baseline challenge, e.g. if reaction occurred at 100 mg of peanut (25 mg of peanut protein), the start dose will be 6 mg. Four doses will be given at the study center with 20-30 min intervals with 0.8, 1.5, 3 and 6 mg of peanut protein. The patient will be observed for 90 minutes after the last dose. If the last dose of peanut protein is tolerated (in the example 6 mg), this dose will be ingested daily at home for 4 weeks (Table 3) in the form of peanut flour mixed with oat flour for the lower doses and Bamba (a peanut-coated corn puff that dissolves in the mouth and contains about 50% peanut protein) from dose 32 mg peanut protein. The study participants are provided from the study center with peanuts in the appropriate form and quantity.

The families receive information on how to fill in a diary at home, which records daily intake of peanut, adverse events (all symptoms that occur during the study period regardless of whether they can be associated with peanut intake) and drugs that the child receives during the study period. The diary is filled in by the parents between the visits and taken to all visits where the study physician goes through the diary together with a parent/the parents.

All study participants will get an "emergency kit", adrenaline autoinjector for intramuscular injection, antihistamine, and b2-agonist for inhalation if the participant has a known asthma. Oral corticosteroids will be provided if the family lives far away from hospital; corticosteroids take 2-3 hours before effect. The parents receive written instruction and a practical demonstration on how/when to use the medications. They will also get instructions on when to contact the study team and/or make an acute hospital visit.

All study participants are instructed to strictly avoid any other intake of peanuts, apart from the OIT doses.

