#### **Visit 4-14\*, week 4-40 (-60), duration 2 hours/visit: up-dosing OIT peanut**

The patient comes for up-dosing according to Table 3 with a predefined increase of peanut protein every 4-6th week up to 285 mg, maintenance dose (= 1.3 peanut = 3 pieces of Bamba), or the dose reached by the child after 60 weeks of up-dosing.

A physical examination is conducted, and a standardized questionnaire is filled in by the physician regarding physical status before the start of up-dosing. The diary is collected and reviewed. Only if the child has fully tolerated the previous dose and has not had any allergic side effects the last week, up-dosing is performed. The up-dosing is performed under the supervision of a research nurse and a physician at the study center. The child is observed for 90 minutes after the dose. The families/patients are informed about co-factors for allergic reactions e.g. high physical activity 3 hours after the dose intake. The up-dosing phase is ongoing for 40-60 weeks. If the patient becomes ill or cannot come to the study center after 6 weeks, the same dose is maintained until a new visit for up-dosing is made. If allergic reactions occur, the dose is changed according to Table 4. If for some reason (such as acute illness) the patient fails to take his/her OIT, the dose will change according to Table 5.

Between all the visits the families can contact the study nurse by telephone or mail if needed. If a moderate/severe allergic reaction/adverse event occurs during on-call time, the families are referred to one of Stockholm's children's emergency wards which will be informed about the study. Material for fecal samples is provided at visit 14.

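### Table 3b, steps 8 and 9: flour and peanut amounts correspond to about 48 and 71–72 mg protein, not the stated 32 and 48 mg, and the % increase at steps 8 and 10 is wrong

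*Protocol*

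**What the plan says.** The section on Visits 4–14 sends staff to this table. It prescribes "up-dosing according to Table 3 with a predefined increase of peanut protein every 4-6th week up to 285 mg".

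Table 3b gives, per step, the protein dose, the weight of flour mix (column header: "Amount of peanut flour 10%* in mg (4,6% peanut protein"), the weight of peanuts, the pieces of Bamba and a % increase. Its footnote defines the mix: "Mix 1g Peanut powder with 9g oat flour". Table 3a, for the first day, has the same 4.6% flour header and the same footnote.

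The section Intervention substance says which product is used when. Flour serves the lower doses. "For higher OIT doses (from 32 mg peanut protein) and the maintenance dose we will use" Bamba. The Visit 3 section repeats the switch at 32 mg.

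**The concern.** The columns of a dosing table are alternative ways of measuring out the same dose, so each row should describe one dose. Rows 8 and 9 describe two. Protein and Bamba follow 24, 32, 48, 95 mg from step 7 to step 10. Flour and peanuts follow about 24, 48, 71, 95 mg, and the % increase column goes with them.

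The children were 12–47 months old at entry and had reacted to peanut at a baseline challenge. Anyone who measured flour or peanuts at step 8 or 9 would give about one and a half times the intended protein. The mislabelled increase matters differently. The move from step 9 to step 10 is a doubling of Bamba, but the table presents it as a rise of one third.

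**Working it through.** **Inputs.** All are from Table 3b, except the Bamba value. That is 95 mg per piece: step 10 equates one piece with 95 mg, and the Visits 4–14 section equates 285 mg with 3 pieces (285/3 = 95).

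| Step | Protein, mg | Flour mix, mg | Peanuts, mg | Bamba, pieces | Printed % increase |
|---|---|---|---|---|---|
| 7 | 24 | 533 | 88 | – | 100 |
| 8 | 32 | 1067 | 176 | 1/3 | 100 |
| 9 | 48 | 1578 | 264 | 1/2 | 50 |
| 10 | 95 | 2111 | 352 | 1 | 33 |

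**1. Ratios within rows.** This check assumes no flour strength.
- Protein/flour at steps 4–7: 3/67 = 4.48%, 6/133 = 4.51%, 12/267 = 4.49%, 24/533 = 4.50%.
- Protein/flour at steps 10–14: 95/2111, 144/3200, 190/4222, 238/5289 and 285/6333 are each 4.50%.
- Protein/flour at step 8: 32/1067 = 3.00%. At step 9: 48/1578 = 3.04%.
- Protein/peanuts in the nine other rows: 27.0–27.3% (for example 24/88 = 27.3%, 95/352 = 27.0%).
- Protein/peanuts at step 8: 32/176 = 18.2%. At step 9: 48/264 = 18.2%.

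Two separate columns fail in the same two rows by about the same factor.

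**2. What the flour and peanut entries amount to.**
- Flour scaled from step 7: 1067/533 × 24 = 48.0 mg; 1578/533 × 24 = 71.1 mg.
- Flour scaled from step 10: 1067/2111 × 95 = 48.0 mg; 1578/2111 × 95 = 71.0 mg.
- Peanuts scaled from step 7: 176/88 × 24 = 48.0 mg; 264/88 × 24 = 72.0 mg.
- Peanuts scaled from step 10: 176/352 × 95 = 47.5 mg; 264/352 × 95 = 71.3 mg.
- Bamba: 1/3 × 95 = 31.7 mg; 1/2 × 95 = 47.5 mg. These match the stated doses.

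Excess over the stated dose:
- flour at the rows' 4.5%: 48.0/32 = +50% and 71.0/48 = +48%;
- flour at the header's 4.6%: 49.1/32 = +53% and 72.6/48 = +51%;
- peanuts at 27%: 47.5/32 and 71.3/48, both about +48%;
- Bamba: none.

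**3. The % increase column.** Formula: dose at this step / dose at the previous step − 1.

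| Step | Printed | From stated protein | From peanuts | From flour |
|---|---|---|---|---|
| 8 | 100 | 32/24: 33 | 176/88: 100 | 1067/533: 100 |
| 9 | 50 | 48/32: 50 | 264/176: 50 | 1578/1067: 48 |
| 10 | 33 | 95/48: 98 | 352/264: 33 | 2111/1578: 34 |

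The printed values reproduce exactly from the peanut column. Step 9 fits both sequences, so the evidence lies in steps 8 and 10.

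**4. Could a shifted cell explain it?** No. The 1067 mg at step 8 would suit 48 mg (48/0.045 = 1067), but 1578 mg flour and 264 mg peanuts mean about 71 mg, a dose that appears nowhere in the protein column.

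**5. Flour strength across Tables 3a and 3b.** For 3 mg, Table 3a gives 65 mg flour (65 × 0.046 = 2.99) and Table 3b gives 67 mg (67 × 0.045 = 3.02). For 6 mg they give 130 and 133 mg. Both headers print 4.6%, but the Table 3b rows use 4.5%, a difference of about 2%.

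**The case against.** The strongest reply is that the wrong cells instruct nobody. From 32 mg the product is Bamba, and the Bamba and protein cells at steps 8 and 9 agree. Whole peanuts are not named as the study product at any step. Stepping back under Table 4 leads either to Bamba at step 8 or above, or to flour at step 7 or below, where the rows are consistent. The % increase is a derived label that sets no dose. All of this stands, and it makes the point minor. What remains is that the protocol refers staff to this table, and the errors sit exactly where the product changes from flour to Bamba.

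A reader might infer more in four ways. The documents do not support these readings.

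- **That children are overdosed by half at steps 8 and 9.** This needs a product that the protocol does not assign there.
- **That the schedule is unsafe at step 10.** The rise from half a piece to one is a doubling, as at steps 5–7, and up-dosing is supervised by a nurse and a physician with 90 minutes of observation.
- **That the excess is larger still.** Intervention substance describes the flour as "50% protein content, Sukrin, Oslo, Norway) mixed with oat flour"; mixed 1 g with 9 g that gives 0.50/10 = 5.0%. This would raise every Table 3b flour row by about 11% (5.0/4.5), so it is a separate discrepancy and does not belong in the size of the error at steps 8 and 9.
- **That the Bamba header is wrong.** "Pieces of Bamba (700mg/piece, protein content 17,5"% gives 700 × 0.175 = 122.5 mg per piece against the 95 mg used in the rows. The header does not say whether this is total or peanut protein, so no error is shown. The two descriptions of Bamba, "a peanut-coated corn puff that dissolves in the mouth and contains 50% peanut and used in the LEAP study" and "a peanut-coated corn puff that dissolves in the mouth and contains about 50% peanut protein", differ in wording, but the rows do not depend on either.

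**Conclusion.** The inconsistency is real and confined to six cells: flour and peanuts at steps 8 and 9, and % increase at steps 8 and 10. The flour and peanut amounts are roughly 50% too high for the stated 32 and 48 mg. The printed increases of 100 and 33 should be 33 and 98. Neither 4.5% nor 4.6% flour removes the mismatch.

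The intended sequence can be read from the document. The text twice names 32 mg as the dose at which Bamba begins, and 32, 48 and 95 mg agree with the Bamba column. With Bamba as assigned, the dose is correct; the only remaining effect is a doubling at step 10 labelled as +33%. The 285 mg maintenance dose, the sample size and the primary outcome are untouched. Severity is minor.

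This rests on the ratios in the other nine rows and on 95 mg per piece of Bamba. The Visit 3 section converts peanuts at 25% (100 mg to 25 mg) instead of about 27%. At that rate the peanut entries would give 44 and 66 mg, which still do not match 32 and 48 mg.

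**What to change.** Keep 32, 48 and 95 mg at steps 8–10 and change six cells in Table 3b:

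- **Flour, steps 8 and 9:** about 711 and 1067 mg at 4.5% (32/0.045, 48/0.045), or 696 and 1043 mg at 4.6% (32/0.046, 48/0.046).
- **Peanuts, steps 8 and 9:** about 119 and 178 mg (32/0.27, 48/0.27).
- **% increase:** 33 at step 8 and 98 at step 10.

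Separately, settle one flour strength against the product label and use it in Tables 3a and 3b. Choosing 4.5% changes both headers and the Table 3a flour cells. Choosing 4.6% lowers the remaining Table 3b flour cells by about 2%. No visit, sample size or outcome changes.

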**Table 4. Action in dose-related symptoms outside the study center**

|                                                                                                                                                                                                                                                                                                                                                                                                                              |
|------------------------------------------------------------------------------------------------------------------------------------------------------------------------------------------------------------------------------------------------------------------------------------------------------------------------------------------------------------------------------------------------------------------------------|
| 
Mild symptoms 1: If the study physician considers the dose tolerated (e.g. only mouth itch), the patient may continue at the same dose at home. The dose can be divided into 2 doses (with 8-12 hours between). The patient may continue on this dose for another 1-2 weeks before dose increase.
                                                                                                              |
| 
Mild symptoms 2: If the study physician considers the dose as not tolerated the next dose should be reversed 1-2 steps and given at the study center.
                                                                                                                                                                                                                                                          |
| 
Moderate symptoms: The next dose should be given at the study center. Reverse 1-2 dose steps and continue at the lower dose until the patient has no or only mild symptoms.
                                                                                                                                                                                                                                    |
| 
Severe symptoms 1 (max. 1 dose of adrenaline have been given): The next dose should be given at the study center. Reverse 2 dose steps. If no symptoms, continue with the lower dose in 2 weeks before the dose increase. If moderate or severe symptoms also occur at this dose, the patient should discontinue the treatment.
                                                                                |
| 
Severe symptoms 2 (2 doses of adrenaline have been given): The next dose should be given at the study center. Reverse 2 dose steps. If this works, continue with the lower dose in 6-8v before the next dose increase. If no symptoms, continue with the lower dose in 2 weeks before the dose increase. If moderate or severe symptoms also occur at this dose, the patient should discontinue the treatment.
 |

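### After a first intensive-care reaction to a home dose during up-dosing, Table 4's written default is to re-dose and increase again; no individual stop is required

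*Protocol*

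**What the plan says.** The protocol's section on Visits 4-14 governs up-dosing and hands reactions to a table: "If allergic reactions occur, the dose is changed according to Table 4". The table's title limits it to home events: "Action in dose-related symptoms outside the study center".

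Table 4 has two rows for severe reactions, told apart by treatment given: "Severe symptoms 1 (max. 1 dose of adrenaline have been given") and "Severe symptoms 2 (2 doses of adrenaline have been given"). Both call for the next dose at the study center, two steps lower. Both then allow up-dosing to resume: "If no symptoms, continue with the lower dose in 2 weeks before the dose increase". The second row also gives a longer wait: "If this works, continue with the lower dose in 6-8v before the next dose increase". Both end with the same stop: "If moderate or severe symptoms also occur at this dose, the patient should discontinue the treatment".

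Three other sections bear on the point:

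- **Individual stopping criteria.** There are two: the family's wish to leave the intervention, and advice to consider stopping once a child has had more than 2 anaphylactic reactions. Neither grades a reaction by severity.
- **Stopping criteria for the whole study.** These are more than half of patients with at least 2 OIT-related anaphylactic reactions, or a fatal reaction to peanut in Group 1.
- **Exclusion criteria.** A child with earlier life-threatening (intensive-care) anaphylaxis, whatever the trigger, cannot enter.

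**The concern.** The number of adrenaline doses records what was given, and it need not track how grave the reaction became. A child who needed intensive care after one or two doses is handled by the same rows as a child whose severe reaction settled quickly. The protocol already names intensive-care anaphylaxis as a category at entry, but does not use it in the rules for a child on treatment.

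For that child the written path is a supervised re-dose, then daily home doses at the lower level, then renewed increases. A mandatory stop comes only after a second moderate or severe reaction, at the lowered dose. What is at stake is a repeat of a life-threatening reaction in a child aged 1 to 3 years at inclusion, under a rule that leaves the decision to stop after the first one to individual judgement.

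**Working it through.** The protocol states no figure on this point. The check is a trace through the rules, followed by two small calculations.

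**1. Rule trace: one first, non-fatal intensive-care reaction to a home dose during up-dosing**

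| Rule | 0-1 adrenaline dose | 2 adrenaline doses |
|---|---|---|
| Table 4 row | Severe 1 | Severe 2 |
| Next dose | at center, two steps lower | at center, two steps lower |
| Wait before increase, if tolerated | 2 weeks | 6-8 weeks and also 2 weeks |
| Stop required by Table 4 | only on recurrence | only on recurrence |
| Individual stopping criteria | 1 is not more than 2, and the rule is advisory: no stop | same |
| Whole-study criteria | not fatal, and one child is not half the patients: no stop | same |

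More than 2 adrenaline doses has no row, so the trace does not extend there.

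**2. Size of the dose reduction**

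Input: the peanut protein doses in Table 3b (3, 6, 12, 24, 32, 48, 95, 144, 190, 238, 285 mg). Share kept = dose two steps lower / triggering dose.

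| Triggering dose, mg | Re-dose, mg | Share kept |
|---|---|---|
| 12 | 3 | 25.0% |
| 24 | 6 | 25.0% |
| 32 | 12 | 37.5% |
| 48 | 24 | 50.0% |
| 95 | 32 | 33.7% |
| 144 | 48 | 33.3% |
| 190 | 95 | 50.0% |
| 238 | 144 | 60.5% |
| 285 | 190 | 66.7% |

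The median is 37.5%, and 7 of the 9 shares are at or below half. The smallest reductions are at the highest doses. Table 3b has no dose two steps below 3 or 6 mg.

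**3. Earliest return to the triggering dose**

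Two steps down means two increases back. Weeks from re-dose = wait at the lowered dose + one up-dosing interval (4-6 weeks, from the section on Visits 4-14).

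- With the 2-week wait: 2 + 4 = 6 to 2 + 6 = 8 weeks.
- With the 6-8 week wait: 6 + 4 = 10 to 8 + 6 = 14 weeks.

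Both results are conditional. Each increase is supervised at the center and must pass the gate "Only if the child has fully tolerated the previous dose and has not had any allergic side effects the last week, up-dosing is performed". If week 60 of up-dosing arrives first, the child stays at the dose reached by then.

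**The case against.** **The protocol does not force anyone to continue.** This stands. A family that withdraws is using a listed stopping criterion and is not departing from Table 4. Nothing forbids the physician to stop after one reaction. The point is limited to the written default, which is to continue.

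**Safeguards are real.** The re-dose and every increase are supervised, the gate must be met, recurrence at the lowered dose ends treatment, and families hold an emergency kit with an adrenaline autoinjector. This lowers the risk. It does not supply a stop after the first event.

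**The entry exclusion proves little.** A reader might infer that the sponsor judged one intensive-care reaction too dangerous for OIT, and so contradicts itself in Table 4. The protocol does not support that. It gives no reason for the exclusion, which applies before randomization to future Group 2 children as well, and which also keeps such children out of the baseline and later challenges. Entry and stopping rules may differ. The exclusion shows only that the category is already in use.

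**Part of the protocol was not available.** The text between Data Collection and Table 1 was not seen here and could hold further safety provisions. That limits confidence.

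**The case is narrow.** It needs intensive care and at most 2 adrenaline doses, and the protocol gives no frequency. That limits how often the gap matters, but not how serious it is when it does.

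**Table 4 has a plainer fault.** The 2-adrenaline row states two incompatible waits. This stands, and a repair that left the row unchanged would be incomplete.

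**Conclusion.** The point holds as a weakness in the individual safety rules and should be repaired. In the text available for review, no rule requires OIT to stop after a first intensive-care reaction to a home up-dosing dose treated with at most 2 adrenaline doses. The stated path keeps 25% to 67% of the triggering dose and may lead back to that dose.

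A reader might go further and conclude that the child is bound to return to the triggering dose. That does not follow: the gate or week 60 may prevent it. Nor does the point show bias in the analysis; it concerns patient safety only.

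The conclusion rests on these assumptions: an intensive-care reaction counts as severe under Table 4; the 'v' in the longer wait means weeks; and no provision in the unseen text overrides Table 4. It is confined to up-dosing, because the section on the maintenance visits does not cite Table 4. The number of such events is unknown and probably small among the 50 planned Group 1 children. Confidence is medium.

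**What to change.** Add one item to the individual stopping criteria, and repeat it as an overriding top row of Table 4:

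*OIT is discontinued after any OIT-related life-threatening (intensive-care) anaphylaxis, at home or at the center; the child stays in the study for observation.*

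In the same edit, delete the 2-week sentence from the 2-adrenaline row, so that the 6-8 week wait alone applies, and write out weeks.

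**Cost.** No procedures are added. A few children may stop OIT early. If each counts as a failure, each lowers Group 1 success by at most 1/50 = 2 percentage points. As an assumed range, take 1, 2 or 3 such children, all of whom would otherwise have succeeded. The 50% success rate in the protocol's power calculation then becomes 48%, 46% or 44%. Power against 10% in Group 2, at the planned 50 and 25 children (Fisher exact, two-sided 5%), goes from 96.0% to 94.2%, 91.7% or 88.5%. All of these stay above the planned 80%.
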